### Patients' inclusion criteria

Patients have to fulfil the following inclusion criteria:

Age between 18 and 65 years.Diagnosis of schizophrenia, schizoaffective disorder, delusional disorder, other psychotic disorders, major depressive disorder, or bipolar disorder according to the DSM-5 and confirmed by the Structured Clinical Interview for DSM-5 (SCID-5) (27).Ability to provide written informed consent.BMI ≥ 25.

### Patients' exclusion criteria

Patients are excluded from the study if they meet one of the following exclusion criteria:

Inability to perform moderate physical activity (i.e., walking at least 150 min per week, or 75 min of vigorous activity twice a week, according to the guidelines of the Italian Ministry of Health).Pregnancy or breast-feeding.Intellectual disability or severe cognitive impairment.Worsening of clinical status or hospital admission in the previous 3 months.

### Blinding

Researchers and statisticians involved in patients' assessments are blinded to patient's allocation. Patients and health professionals providing the interventions are not blinded to patient allocation.

## Interventions

### Arm I: lifestyle psychosocial group intervention

The theoretical background of the new psychosocial group intervention includes techniques derived from classic psychoeducation (28), motivational intervention (29–31), and cognitive-behavioral therapy (32).

The intervention has been developed following the guidelines on the management of physical health in people with mental disorders produced by the World Health Organization (33, 34), the European Association for the Study of Diabetes (35), the European Society of Cardiology (36), and the European Psychiatric Association (37).

The adopted methodology included the following phases: (1) analysis of the scientific literature; (2) evaluation of available handbooks and manuals on other psychosocial interventions targeting lifestyle behaviors; (3) focus groups with expert researchers and clinicians, and with users and carers, in order to identify the most relevant needs to be included in the intervention; (4) development of *ad-hoc* manuals by the research group with a detailed description of each session of the intervention. Manuals have been developed in order to ensure treatment fidelity among the different centers. Leaflets and other written materials are given to patients, whenever relevant.

The intervention lasts 5 months and it is administered to groups of 5–10 patients every 7–10 days. The sessions cover the following topics: (1) healthy diet; (2) physical activity; (3) smoking habits; (4) medication adherence; (5) risky behaviors; (6) promotion of circadian rhythms. Each module includes the following components: (a) information on the risks of the specific unhealthy lifestyle and benefits in adopting healthy lifestyle; (b) teaching of practical strategies to change unhealthy behaviors; (c) identification of personal life goals for each participant, motivation to change, and problem-solving strategies. Sessions have been developed in order to stimulate discussion, work-groups and interaction among participants. At the end of each meeting, a 20-min session of moderate physical activity is scheduled (Table 1). The core feature of this intervention is the inclusion of the motivational component. During each session, group participants are supported by mental health professional in identifying a personal healthy lifestyle goal. After goal-definition, professionals help participant to define the motivations for lifestyle changing and teach problem-solving strategies for sustaining the behavioral change.

**Table 1 T1:** Programme of LIFESTYLE psychosocial group intervention.

Starting session: Introduction of the intervention, aims, purposes, presentation of participants, and definition of personal healthy lifestyle goals
Module 1: Diet, information on health food, principles, and benefits of healthy eating
Module 2: Physical activity, how to increase routine physical activity
Module 3: Smoking habits, information on the dangers of smoking, craving, difficulties for quitting smoking and consequences of long-term abuse of nicotine.
Module 4: Medication adherence, strategies for improving adherence, medical consequences of non-adherence
Module 5: Risky behaviors, sexually transmitted disorders, substance, and alcohol abuse
Module 6: Promotion of regular circadian rhythm, problems related to irregular daily activities
At the end of each meeting, a 20-min session of moderate physical activity (i.e., walking) is implemented with participants
Information and leaflets are provided to participants during each session. Positive changes are highlighted, potential strategies for change are discussed at each module. The core feature of the intervention is the inclusion of the motivational component. During each session, group participants are supported by mental health professionals in identifying a personal healthy lifestyle goal. After goal-definition, professionals help participant to define the motivations for lifestyle changing and teach problem-solving strategies for sustaining the behavioral change

### Arm II: brief educational group intervention

The brief educational group intervention, which includes elements from the psychoeducational approach and from problem-solving techniques, consists of 5 weekly sessions and it is administered to groups of 5–10 patients. The following topics are covered: (1) healthy lifestyle; (2) early detection of clinical relapses; (3) effects of pharmacological treatment and management of side effects; (4) stress management techniques; (5) problem-solving techniques.

Manuals have been developed in order to ensure treatment fidelity among the different centers. Leaflets and other written materials are given to patients, whenever relevant. During the sessions, interaction among participants is supported using role-plays and work-groups (Table 2).

**Table 2 T2:** Programme of LIFESTYLE educational brief group intervention.

Starting session: Introduction of the intervention, aims, purposes, and presentation of participants
Module 1: Healthy lifestyle (e.g., healthy diet, physical activity, smoking habits, promotion of circadian rhythm)
Module 2: Early detection of psychiatric relapses
Module 3: Pharmacological treatment and management of side effects
Module 4: Stress management techniques
Module 5: Problem-solving techniques
Information and leaflets are provided to participants during each session. Positive changes are highlighted, potential strategies for change are discussed at each module. The main aim is to provide patients with the principles of healthy living (i.e., eating fruit and vegetable, drinking water, doing moderate physical activities, not abusing of alcohol, quit smoking, etc.)

## Training of mental health professionals

For each participating center, three mental health professionals (at least one being a psychiatrist) participated to a 5-day training course for the provision of the two interventions, held in Naples in June 2017. Supervision meetings are organized during the study period as well as regular phone and e-mail supervisions.

## Ethical issues

This study is being conducted in accordance with globally accepted standards of good practice, in agreement with the Declaration of Helsinki and with local regulations.

The study investigators ensure that all mental health professionals involved in the study are qualified and informed about the protocol, interventions, and trial-related duties. The coordinating center has a list of all qualified mental health professionals involved in the study.

A formal ethical approval for conducting the trial has been obtained by the Coordinating Center's Ethics Committee, which approved the whole study protocol on January 2017 (approval number: prot. 64).

## Assessment time and instruments

Researchers participating to the study are blinded to patient allocation. All patients are assessed at the following time points: baseline (T0); 2 months post-randomization (T1); 4 months post-randomization (T2); 6 months post-randomization (T3); 12 months post-randomization (T4); and 24 months post-randomization (T5). T1 and T2 assessments include only anthropometric tests. All data will be collected through a paper and pencil interviewing and the expected time for filling in all assessment tools is about 60/90 min. During the completion of the assessment battery, whether patients feel distressed or exhausted, the assessment can be stopped and another appointment will be scheduled in the next 2/3 days with the researcher.

The following questionnaires and schedules will be used during the study (Table 3):

The Food Frequency Questionnaire—short version (38) is a 18-item questionnaire on the frequency of consumption of a variety of foods corresponding to one's usual diet. In order to compile the questionnaire, the Scotti-Bassani Atlas is used for selecting quantity of food.The International Physical Activity Questionnaire (IPAQ)—short form (39) is a 18-item questionnaire exploring physical activity in terms of time spent in walking, in moderate-intensity and vigorous-intensity activities.The Fagerström Test for Nicotine Dependence (FTND) (40) is a 6-item questionnaire assessing the intensity of physical addiction to nicotine in terms of number of cigarette smoked per day, compulsion to use, and nicotine addiction.The Pittsburgh Sleep Quality Index (PSQI) (41) is 19-item questionnaire assessing sleep quality over a 1-month time interval.The Leeds Dependence Questionnaire (LDQ) (42) is a 10-item questionnaire designed to measure dependence for a variety of substances.The Morisky Medication Adherence Scale (MMAS) (43) is a 4-item questionnaire for evaluating adherence to pharmacological treatments.The Cumulative Illness Rating Scale (CIRS) (44) is a 14-item questionnaire including a comprehensive assessment of physical comorbidities.The Manchester Short Assessment of Quality of Life (45) is a 17-item questionnaire assessing quality of life focusing on satisfaction with life as a whole and with life domains.The Recovery Style Questionnaire (RSQ) (46) is a 39-item self-report questionnaire exploring six styles of adaptation to severe mental disorder and recovery: sealing over, tends toward sealing over, mixed picture in which sealing over predominates, mixed picture in which integration predominates, tends toward integration, and integration.The Measurement and Treatment Research to Improve Cognition in Schizophrenia (MATRICS) Consensus Cognitive Battery (MCCB)—brief version, which includes the MATRICS Consensus Trail Making Test—part A, Brief Assessment of Cognition in Schizophrenia: Symbol Coding, Category Fluency-Animal Naming (47, 48).Internalized Stigma of Mental Illness (ISMI), a 29-item questionnaire for evaluating the experience of stigma and internalized self-rejection (49). Each item is rated on a 4-level Likert scale, where higher scores indicate greater levels of internalized stigma.Questionnaire on lifestyle behaviors, a 24-items questionnaire, developed by the Italian National Institute of Health, which evaluates dietary patterns (e.g., food eaten at breakfast or lunch time), smoking habits (e.g., numbers of cigarettes smoked per day; attempts to quit smoking), and physical activity (e.g., time spent in walking per day) (50).The Questionnaire on sexual health, it is a 13-item *ad-hoc* questionnaire developed by the research team, which evaluates sexual behaviors and attitudes.The Pattern of Care Schedule (PCS)—modified version (51), a 40-item questionnaire on pharmacological and non-pharmacological treatments as well as on health care access made by the patient. It is compiled by the researcher in collaboration with the patient. If information is inadequate, or if the researcher is not sure about patients' reliability, other sources (e.g., treating physician, relatives, etc.) can be consulted. During the study period, the treating clinician will continue to provide the usual treatment to patient, and—if necessary—to change or adjust the pharmacological regimen.The anthropometric schedule is compiled by the researcher for collecting information on weight, height, BMI, waist circumference, blood pressure, resting heart rate, HDL, LDL, and overall level of cholesterol, blood glucose, triglycerides, and blood insulin. Moreover, the homeostatic model assessment (HOMA) index will be calculated for quantifying insulin resistance and beta-cell functioning as well as the Framingham Risk Score, for evaluating cardiovascular risk.

**Table 3 T3:** Assessment tools and time-points of the evaluation.

**Assessment tool**	**Domains covered**	**Assessments' timepoints**					
		**T0 (baseline)**	**T1 (2 months)**	**T2 (4 months)**	**T3 (6 months)**	**T4 (12 months)**	**T5 (24 months)**
Pattern of Care Schedule (PCS)—modified version	A 40-item questionnaire on pharmacological and non-pharmacological treatments as well as on health care access made by the patient. It is compiled by the researcher in collaboration with the patient. If information is inadequate, or if the researcher is not sure about patients' reliability, other sources (e.g., treating physician, relatives, etc.) can be consulted	x			x	x	x
Socio-demographic schedule	Information were collected: age, gender, marital status, level of education, working condition, economic status, number of family members, illness duration, time in charge at the mental health centre (months), number of (voluntary and involuntary) hospitalizations, suicide attempts (numbers)	x					
Anthropometric schedule	It is compiled by the researcher for collecting information on weight, height, BMI, waist circumference, blood pressure, resting heart rate, HDL, LDL and overall level of cholesterol, blood glucose, triglycerides and blood insulin. Moreover, the homeostatic model assessment (HOMA) index will be calculated for quantifying insulin resistance and beta-cell function as well as the Framingham Risk Score, for evaluating cardiovascular risk	x	x	x	x	x	x
Structured Clinical Interview for DSM-5 (SCID-5)	It is a semi-structured interview guide for making DSM-5 diagnoses. It is administered by a trained mental health professional that is familiar with the DSM-5 classification and diagnostic criteria	x					
Measurement and Treatment Research to Improve Cognition in Schizophrenia (MATRICS) Consensus Cognitive Battery—brief version	It includes the MATRICS Consensus Trail Making Test—part A, Brief Assessment of Cognition in Schizophrenia: Symbol Coding, Category Fluency-Animal Naming (45, 46)	x			x	x	x
Brief Psychiatric Rating Scale (BPRS)	It is a semi-structured 24-item interview on psychopathological status. The items are grouped in four subscales: positive symptoms, negative symptoms, depressive-anxiety symptoms, and manic-hostility symptoms	x			x	x	x
Cumulative Illness Rating Scale (CIRS)	It is a 14-item questionnaire including a comprehensive assessment of physical comorbidities	x			x	x	x
Fagerström Test for Nicotine Dependence (FTND)	It is a 6-item questionnaire assessing the intensity of physical addiction to nicotine in terms of number of cigarette smoked per day, compulsion to use, and nicotine addiction	x			x	x	x
Food Frequency Questionnaire—short version	It is a 18-item questionnaire on the frequency consumption of a variety of foods corresponding to one's usual diet. In order to compile the questionnaire, the Scotti-Bassani Atlas is used for selecting quantity of food	x			x	x	x
Internalized Stigma of Mental Illness Inventory	It is a 29-items questionnaire for evaluating the subjective experience of stigma	x			x	x	x
International Physical Activity Questionnaire (IPAQ)—short form	It is a 18-item questionnaire exploring physical activity in terms of time spent in walking, in moderate-intensity and vigorous-intensity activities	x			x	x	x
Questionnaire on sexual health	It is an ad-hoc questionnaire developed by the research team, which evaluates sexual behaviours and attitudes	x			x	x	x
Leeds Dependence Questionnaire (LDQ)	It is a 10-item questionnaire designed to measure dependence for a variety of substances	x			x	x	x
Manchester Short Assessment of Quality of Life	It is a 17-item questionnaire assessing quality of life focusing on satisfaction with life as a whole and with life domains	x			x	x	x
Morisky Medication Adherence Scale (MMAS)	It is a 4-item questionnaire for evaluating adherence to pharmacological treatments	x			x	x	x
Personal and Social Performance Scale	It is a 100-point single-item rating scale, subdivided into 10 equal intervals. The ratings are based mainly on the assessment of patient's functioning in four main areas: (1) socially useful activities; (2) personal and social relationships; (3) self-care; and (4) disturbing and aggressive behaviours	x			x	x	x
Pittsburgh Sleep Quality Index (PSQI)	It is 19-items questionnaire assessing sleep quality over a 1-month time interval	x			x	x	x
Questionnaire in lifestyle behaviours	It consists of 24 items, which evaluates dietary patterns (e.g., food eaten at breakfast or lunch time), smoking habits (e.g., numbers of cigarettes smoked per day; attempts to quit smoking), physical activity (e.g., time spent in walking per day)	x			x	x	x
The Recovery Style Questionnaire (RSQ)	It is a 39-item self-report questionnaire exploring six styles of adaptation to severe mental illness and recovery: sealing over, tends toward sealing over, mixed picture in which sealing over predominates, mixed picture in which integration predominates, tends towards integration, and integration	x			x	x	x
ECG evaluation		x					

The following semi-structured interviews will be used during the study:

The Brief Psychiatric Rating Scale (BPRS) (52) is a semi-structured 24-item interview on psychopathological status. The items are grouped in four subscales: positive symptoms, negative symptoms, depressive-anxiety symptoms, and manic-hostility symptoms.The Personal and Social Performance Scale (53) is a 100-point single-item rating scale, subdivided into 10 equal intervals. The ratings are based mainly on the assessment of patient's functioning in four main areas: (1) socially useful activities; (2) personal and social relationships; (3) self-care; and (4) disturbing and aggressive behaviors.The Structured Clinical Interview for DSM-5 (SCID-5) is a semi-structured interview guide for making DSM-5 diagnoses. It is administered by a trained mental health professional that is familiar with the DSM-5 classification and diagnostic criteria.

The inter-rater reliability among researchers participating in the study was tested through Cohen's Kappa coefficient during the training course on the assessment instruments (54). Case-vignettes, videos and role-play have been used in order to ensure fidelity. The Cohen's kappa values were found to be satisfactory for PSP with a value of 0.918 and for the BPRS with a value from 0.835 to 0.972. For the SCID-5, 100% agreement rate was found.

## Anticipated results

### Primary outcome

BMI has been selected as primary outcome since it is a reliable and feasible anthropometric parameter, and it has already been considered in previous studies on lifestyle interventions (15, 16, 24). The primary outcome is the change of the BMI at 6 months post-randomization (T3). We expect a mean difference between the two groups of at least one point (and standard deviation of 2 points) at BMI. The work hypothesis is that the LIFESTYLE psychosocial group intervention will be more effective than the brief educational group intervention in reducing the BMI.

### Secondary outcome

The secondary outcomes include an improvement in dietary patterns (i.e., a reduction in fat food and increase in consumption of fruits and vegetables), smoking habits (i.e., a reduction in the number of cigarettes smoked per day), sleeping habits (i.e., regular number of hours slept per night), physical activity (i.e., increasing in time spent walking per day), personal and social functioning (i.e., level of functioning and time dedicated to meeting friends), severity of physical comorbidities (i.e., reduction at the CIRS global score), and adherence to medications (i.e., reduction in changes in pharmacological doses and regimen).

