### Patients' recruitment

Patients are being recruited in six outpatient units from the universities of Naples, Bari, Genova, L'Aquila, Pisa, and Rome—Tor Vergata.

Eligible patients are identified by their clinicians and referred to the LIFESTYLE research staff by phone, email, or in-person contact. After the patients have been contacted, a meeting is arranged at the outpatient clinic with the referring clinician and the LIFESTYLE staff. Verbal and written information about the project are provided. If the patient accepts to participate to the study, an informed consent form is signed and an appointment for baseline assessment is made. Once the informed consent is collected, the patient is formally enrolled in the study's protocol. Before starting the baseline assessment, the LIFESTYLE staff member contacts the statistician working at the Coordinating Center for obtaining the randomization code for patients' group allocation. The randomization procedure is stratified according to center, age, gender, and educational level with a 1:1 ratio. The treating psychiatrist will continue to provide the usual treatment to patients.

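### The medication adherence outcome is defined by changes in doses and regimen, which largely reflect prescribing, so it is a poor proxy for adherence

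*Protocol article*

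**What the plan says.** The Secondary outcome section lists seven outcomes, each followed by a gloss in parentheses. The last is "adherence to medications (i.e., reduction in changes in pharmacological doses and regimen". The gloss opens with i.e., so it reads as the definition and not as an example.

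Two places say who manages drug treatment during the trial. Patients' recruitment states: "The treating psychiatrist will continue to provide the usual treatment to patients". Assessment time and instruments, within the entry for the Pattern of Care Schedule (PCS), states: "the treating clinician will continue to provide the usual treatment to patient, and—if necessary—to change or adjust the pharmacological regimen".

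The same section lists an instrument whose stated purpose is adherence: "The Morisky Medication Adherence Scale (MMAS) (43) is a 4-item questionnaire for evaluating adherence to pharmacological treatments". Table 3 schedules it at T0, T3, T4 and T5. The PCS, which records treatments, is scheduled at the same four visits.

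Under Data analysis, the named outcome variables of the GEE model are BMI, the CIRS severity index, abdominal circumference, laboratory values, blood pressure and cigarettes per day. None of them measures adherence.

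**The concern.** Adherence is what the patient does with a prescription. A change of dose or regimen is, in the article's own account of usual care, something that the clinician does to the prescription. The two can move independently, and the definition scores the second while carrying the name of the first.

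The article presents adherence as a target of the experimental arm. Table 1 gives it a module of its own, and the Discussion names better adherence among the needs that the intervention was built to meet. A result on this outcome would be read as evidence on that aim. If it mostly tracks prescribing, it could show a benefit where patients take their drugs no better, or hide one where they do.

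**Working it through.** The protocol gives no figure for this outcome, so there is nothing to recompute. The check sets the definition beside the document's other statements.

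**Step 1. What is counted.** The definition counts changes in doses and regimen, and fewer is better. It does not say whose changes count.

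**Step 2. Who makes such changes.** The only statement in the article about who changes the regimen during the study names the treating clinician, and its terms are close to those of the outcome: "to change or adjust the pharmacological regimen". Nothing excludes these changes from the count.

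**Step 3. How patients are scored.** Take four patients with the same number of changes before the trial, and apply the definition literally.

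| Takes the drug as prescribed | Prescription during follow-up | Counted by the definition | Actual adherence |
|---|---|---|---|
| Yes | Unchanged | No change | Good |
| Yes | Adjusted by the clinician | Change, so worse | Good |
| No | Unchanged | No change | Poor |
| No | Adjusted by the clinician | Change, so worse | Poor |

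The score follows the second column and not the first. Rows 1 and 3 score alike although adherence differs. Rows 1 and 2 score differently although adherence is the same. Row 3 is not scored as an improvement: the outcome is a reduction in changes, and a patient with none before and none after shows no reduction. That patient simply scores no worse than an adherent one.

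**Step 4. How the document treats adherence elsewhere.** Table 1 speaks of strategies for improving it, taught to patients. The Discussion treats non-adherence as a cause of relapse and hospitalization. Both treat it as patient behaviour. The type of drug treatment, by contrast, appears under Data analysis among the confounders in the logistic regression.

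**Step 5. Whether a closer measure exists.** The MMAS "is a 4-item questionnaire for evaluating adherence to pharmacological treatments" and is taken at T0, T3, T4 and T5. A change score to T3, T4 and T5 can therefore be formed without new data.

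**Step 6. Whether naming a scale would be out of place.** In the same sentence, physical comorbidity is tied to the CIRS global score, so the section already names a scale where the authors chose to.

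**The case against.** The strongest objection is that the gloss may mean changes that patients make to their own doses or regimen. Most of the neighbouring outcomes (food, cigarettes, sleep, walking, meeting friends) are patient behaviours, and the item is headed as adherence. On that reading, a patient who quietly stops a drug has changed the regimen and counts as worse, and row 3 above reverses. This reading is possible. But the article does not state it, and where it does discuss regimen changes it assigns them to the clinician. The definition needs correcting even if this was the intention.

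A second objection is that a condensed article need not map every instrument to an outcome, and that most of the seven outcomes appear without theirs. That is right: failing to name the MMAS is not in itself a fault, nor is its absence from the GEE list. The fault is the definition that is stated. An analysis plan that used the MMAS instead would depart from it.

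Third, regimen changes may carry some information on adherence, for example when a relapse after non-adherence leads to a new prescription. This stands, and is why the measure is called a poor proxy and not an unrelated one.

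Fourth, patients are not blinded and the experimental arm is taught about adherence. If the MMAS is patient-reported, which the article does not state, the scale may carry reporting bias. This also stands, as a limitation of the remedy.

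**Conclusion.** The definition is badly fixed and should be corrected. Followed as written, it largely measures prescribing and could mislead on adherence. This rests on reading the gloss literally, with clinician changes included because nothing excludes them.

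Its reach is one of seven secondary outcomes. The power calculation is built on BMI alone, so the primary outcome and the sample size are unaffected.

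A reader might infer more, and the document does not support it:

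- **That the outcome is wholly invalid.** Regimen changes may partly follow adherence.
- **That the loss can be expressed as a diluted effect or a larger required sample.** The article gives no correlation between regimen changes and adherence. A dilution formula would also assume that the intervention reaches prescribing only through adherence, which is the very point in doubt.
- **That the bias favours a particular arm.** The brief arm has a module on drug treatment and side effects and the experimental arm has one on adherence. Whether either prompts prescription changes is not known.
- **That the sleep outcome has the same defect.** It is given as "sleeping habits (i.e., regular number of hours slept per night". The PSQI is described as assessing sleep quality, which is a different construct, so no change there follows from this point.

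**What to change.** In Secondary outcome, replace the gloss on adherence with the between-arm difference in change in MMAS score from T0 to T3, and likewise to T4 and T5. Under Data analysis, add the MMAS score to the named GEE outcome variables. Report changes in doses and regimen from the PCS separately, by arm, as concomitant treatment.

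The cost is a change of wording in two sections and one more analysis. No new data, visits or patients are needed, because the MMAS and the PCS are both already scheduled at T0, T3, T4 and T5. State how the MMAS is completed and, if patients report it themselves, acknowledge possible reporting bias in unblinded participants.
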